### Interventions

Both groups will receive a standardized, supervised rehabilitation program consisting of 10 sessions during 1 month (one day in between). Each treatment session in both groups lasted 60 minutes and consisted of three parts: 20 minutes of functional electrical stimulation applied to the quadriceps and tibialis anterior muscles (10 minutes each, 35 Hz frequency, 200–400 µs pulse width, with current intensity producing a clear, painless contraction); 20 minutes of conventional therapeutic exercises—including strengthening of the tibialis anterior, quadricep, gluteal and hamstring to improve stance phase control and functional activities such as sit to stand, step up, push up [6]; and finally, 20 minutes of gait training using parallel bars under therapist supervision.

#### VR‑based gait training group

Participants in the VR group will perform gait training on parallel bars using a virtual reality system. The VR system consisted of a Kinect 2 camera with a motion depth detection range of approximately 5 m, equipped with a moving depth path avatar extraction system. It provided real-time detection and feedback of lower limb joint angles in the sagittal plane, as well as stepping length feedback. VR‑based gait training is delivered in two 10‑minute phases. In the first phase, step length is adjusted using visual cues (green lines) on the VR screen based on the patient’s initial ability, and the patient practices forward and backward parallel walking accordingly (Fig. 1, step lenght). In the second phase, knee and ankle flexion range are adjusted using visual feedback on the screen (Fig. 2, knee and ankle flexion). Training is performed in an open environment, requiring the patient to focus on the VR instructions despite surrounding distractions. tDCS combined with gait training*:* tDCS combined with gait training receive transcranial direct current stimulation simultaneously while walking on the parallel bars for 20 min. The portable and lightweight tDCS device allows stimulation during gait training (Model: Segal Stim AT-12). (Fig. 3, tDCS device). The current intensity is set at 1- 1.5 mA (**as tolerated by the patient),** with the anodal electrode placed over either F3 or F4, depending on the side of the brain lesion, and the cathodal electrode positioned over the contralateral supraorbital area [26]. Typically, stimulation targets the dorsolateral prefrontal cortex (DLPFC), a region associated with the reduction of fear responses [27]. The F3 and F4 locations are identified based on the international 10–20 EEG electrode placement system.

**Fig. 1 fig0001:**
[figure not shown]
Step lenght.

**Fig. 2 fig0002:**
[figure not shown]
Knee and ankle flexion.

**Fig. 3 fig0003:**
[figure not shown]
tDCS device.

In the first session, participants in both groups performed 1 min of parallel walking with therapist guidance to familiarize them with the intervention procedures. To prevent contamination between groups, Treatments will be scheduled on alternating days (odd and even days).

### Methods of measurement

This study uses the Falls Efficacy Scale International (FES-I) questionnaire to assess fear of falling. The questionnaire comprises 16 items, each scored from 1 (not at all concerned) to 4 (very concerned) [28].

The Mini‑BESTest is a shortened version of the BESTest consisting of 14 items that assess dynamic balance, including anticipatory postural adjustments, reactive postural responses, sensory orientation on level and inclined surfaces, and dynamic gait stability. Each item is scored on a 3‑point ordinal scale (0–2), where 0 indicates inability and 2 indicates normal performance [29].

The Biodex Balance System is used to objectively assess balance. Participants stand barefoot with hip‑width foot placement and try to maintain stability near the center. After familiarization at stability level 8, testing is performed at level 6. Three 20‑second trials with 30‑second rest intervals are completed with eyes open, and the mean of the three trials is used for analysis [30].

The 10‑Meter Walk Test (10MWT) assesses walking speed. Participants walk at their self‑selected comfortable speed along a straight, flat, obstacle‑free 10‑meter walkway, and the time to walk between the 2‑ and 8‑meter markers is recorded to calculate walking speed [31].

Before and after the intervention, an independent physiotherapist blinded to group allocation will assess participants. To minimize learning, fatigue, and bias, assessments will be conducted in random order. All data will then be coded (methods as codes 1 and 2) and analyzed using statistical software.

### Statistics

#### Descriptive statistics

Measures of central tendency (mean) and dispersion (standard deviation, variance, and range) were calculated for quantitative variables.

#### Data analysis

data normality will be assessed with the Shapiro–Wilk test. Depending on distribution, paired t‑tests or Wilcoxon tests will be applied for within‑group comparisons, and 2 × 2 repeated‑measures ANOVA will be used for between‑group analyses. Between-group differences were analyzed using ANCOVA, with time since stroke (post-onset duration) included as a covariate to account for potential differences in recovery status. Statistical analyses will be performed in SPSS v26, with significance set at p < 0.05.

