## Abstract

Fear of falling is a prevalent and disabling problem after stroke, contributing to reduced activity, impaired balance, and increased fall risk. Recent studies indicate that virtual reality (VR)–based interventions and transcranial direct current stimulation (tDCS) applied during exercise therapy may help reduce fear of falling in individuals with neurological disorders.

This single‑center, assessor‑blinded randomized controlled trial aims to compare the effects of VR‑based gait training with tDCS combined with gait training on fear of falling in patients with subacute stroke. Participants will be randomly allocated to either the VR or tDCS group, while all also receive conventional physiotherapy. Outcomes will be assessed at baseline and after ten treatment sessions by a blinded assessor. The primary outcome is fear of falling, measured using the Falls Efficacy Scale‑International (FES‑I). Secondary outcomes include balance, assessed by the Mini‑BESTest and Biodex Balance System, as well as walking ability, assessed by the 10‑Meter Walk Test. It is hypothesized that VR‑based gait training will result in a greater reduction in fear of falling than tDCS combined with gait training.

Specifications table

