**Table utbl0001:** 

**Subject area**	Neuroscience
**More specific subject area**	*Fear of falling*
**Name of your protocol**	*Comparing the effect of virtual reality and transcranial direct current stimulation on fear of falling, balance, and walking ability in patients with stroke*
**Reagents/tools**	• The Falls Efficacy Scale International questionnaire • The shortened version of the Balance Evaluation Systems Test • The Biodex Balance System • The 10-Meter Walk Test
**Experimental design**	*Stroke patients will be allocated to two intervention groups, Virtual Reality and transcranial Direct Current Stimulation combined with gait training . All participants will receive conventional physiotherapy also. Group allocation will be performed using block randomization stratified by sex and history of falls. The outcome measures include fear of falling, balance, and walking ability. These variables will be assessed at prior to the initiation of treatment and the day after the last session.*
**Trial registration**	*Registration No.: IRCT20251005067515N1*
**Ethics**	• The study will be conducted in accordance with the Declaration of Helsinki and approved by the Ethics Committee of the University of Social Welfare and Rehabilitation Sciences (IR.USWR.REC.1404.126). • Written informed consent will be obtained, and participants will be informed of study procedures, confidentiality, and their right to withdraw at any time.
**Value of the Protocol**	• To compare the effects of virtual reality versus tDCS during walking on fear of falling in stroke patients. • To evaluate the potential of technology‑assisted rehabilitation to enhance post‑stroke recovery. • To provide clinical evidence on the applicability and effectiveness of VR‑ and tDCS‑based interventions in routine stroke rehabilitation.

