### Inclusion and exclusion criteria

32 stroke patients will be recruited for this study. inclusion criteria: Age between 40 and 70 years [21]. 2. Confirmed diagnosis of unilateral ischemic stroke in the subacute phase (3–6 months post-onset) [6] 3. Ability to walk independently for a minimum of 10 m, potentially with the assistance of a single standard walking aid [22]. 4. Hospital Anxiety and Depression Scale (HADS) score < 16 to ensure participants’ ability to cooperate and to exclude cases of severe depression [23]. 5. Cognitive screening score ≥ 21 on the Mini-Mental State Examination (MMSE) [24]. 6. Spasticity severity of the ankle dorsiflexor group, according to the Modified Ashworth Scale (MAS), on the injured side 2 or less [25]. Exclusion Criteria: 1. Significant orthopedic, vestibular, or cardiovascular conditions precluding safe gait training. 2. Presence of implanted metallic devices, pacemakers, deep brain stimulators. 3. Presence of major neurological comorbidities or psychiatric disorders. Participant recruitment will take place through the inpatient neurological rehabilitation wards of Rofeideh Hospital and affiliated units of URSSH. Throughout all treatment sessions, if the participant experiences severe fatigue, blurred vision, dizziness, or any other unexpected adverse sensation, the intervention will be immediately discontinued. The trial will also be stopped for any participant who shows sensitivity or intolerance to tDCS, expresses unwillingness to continue participation, or develops any of the exclusion criteria during the study period.

A blinded assessor will evaluate outcomes at baseline and after ten physiotherapy sessions, with assessments scheduled to avoid unblinding. The study follows the Declaration of Helsinki, written informed consent will be obtained, and participants’ demographic and clinical information will be recorded after randomization.

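### Significance tests within each arm cannot show that VR or tDCS is effective, because every participant receives one of them on top of the same programme; only the VR-versus-tDCS contrast can be inferred

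*Protocol article*

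**What the plan says.** **Design.** The Abstract describes two active arms on a common background: "Participants will be randomly allocated to either the VR or tDCS group, while all also receive conventional physiotherapy". The Interventions section confirms the background: "Both groups will receive a standardized, supervised rehabilitation program consisting of 10 sessions during 1 month". Each 60-minute session has three parts of 20 minutes. The first is "20 minutes of functional electrical stimulation applied to the quadriceps and tibialis anterior muscles", the second is conventional exercise, and the third is supervised gait training on parallel bars. VR or tDCS is added during the third part. There is no sham arm and no arm with conventional therapy alone.

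**Population.** Participants are in the "subacute phase (3–6 months post-onset" window (Inclusion and exclusion criteria).

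**Hypothesis.** The Abstract states that VR-based gait training "will result in a greater reduction in fear of falling than tDCS combined with gait training". This is a comparative claim.

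**Stated value.** Among the bullets under Value of the Protocol in the specifications table is "To provide clinical evidence on the applicability and effectiveness of" VR- and tDCS-based interventions in routine stroke rehabilitation. The first bullet of the same row is comparative.

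**Analysis.** Within each arm, the Data analysis section plans paired t-tests or "Wilcoxon tests will be applied for within‑group comparisons". For the contrast between arms it names a 2 × 2 repeated-measures ANOVA and an ANCOVA: "Between-group differences were analyzed using ANCOVA, with time since stroke (post-onset duration) included as a covariate". One significance level, p < 0.05, covers all of these. Nothing marks the within-arm tests as descriptive.

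**The concern.** The table bullet speaks of the effectiveness of each kind of intervention. The randomised comparison can only say how VR does relative to tDCS. The within-arm tests are the only planned analyses that could appear to speak to the effect of either add-on taken alone, and they cannot do so. A change from baseline to the post-treatment visit contains:

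- any effect of the add-on;
- recovery that may continue at 3–6 months after stroke;
- the shared therapy, which is 40 of the 60 minutes plus the supervised gait practice itself;
- retest effects on the scale;
- regression to the mean, probably small for the FES-I because the listed entry criteria set no FES-I threshold.

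With no arm free of VR and tDCS, the data cannot separate the first item from the others. The plan itself treats recovery status as a concern, since its ANCOVA adjusts for time since stroke. That adjustment concerns the between-arm comparison and does nothing for the within-arm tests. The Limitations section mentions current spread and sample size, but not this. What is at stake is the set of conclusions that the trial is entitled to draw.

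**Working it through.** The plan gives no figure for the within-arm tests, so there is none to reproduce. The check asks how often such a test is significant when neither add-on does anything.

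**Inputs** (Sample size calculation): SDs 8.4 and 10.8, pre–post correlation 0.6, alpha 0.05, 16 per group. Sidedness is not stated, and two-sided is assumed. I take 16 as given; whether it follows from its own inputs is a separate matter.

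**Assumptions** (mine, not the protocol's): both arms improve by the same amount d from recovery, shared therapy and retest; VR and tDCS add nothing; the SD is equal before and after. The documents give no value for d, so I show 0 to 8 points. The upper end is the difference used for the sample size, 48.9 − 40.9 = 8.0.

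**Step 1, SD of change.** Pooled SD = √((8.4² + 10.8²)/2) = √((70.56 + 116.64)/2) = √93.6 = 9.67. SD of change = 9.67 × √(2 − 2 × 0.6) = 9.67 × √0.8 = 8.65.

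**Step 2, standard error in one arm.** 8.65/√16 = 2.16.

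**Step 3, chance that one arm is significant.** This is p = P(|T| > t₀.₉₇₅,₁₅), where T is noncentral t on 15 degrees of freedom with noncentrality d/2.16. At d = 4 the noncentrality is 1.85 and p = 0.409.

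**Step 4, both arms.** The arms are independent, so at least one is significant with probability 1 − (1 − p)², and exactly one with probability 2p(1 − p). At d = 4 these are 1 − 0.591² = 0.65 and 2 × 0.409 × 0.591 = 0.48.

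| Shared improvement, points | A given arm significant | At least one arm | Exactly one arm |
|---|---|---|---|
| 0 | 5% | 10% | 10% |
| 2 | 14% | 26% | 24% |
| 4 | 41% | 65% | 48% |
| 6 | 74% | 93% | 39% |
| 8 | 93% | >99% | 13% |

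**Sensitivity to dropout.** The plan allows for 15% dropout, and 16 × 0.85 = 13.6. With 13 per arm, a given arm is significant in 5%, 12%, 34%, 63% and 86% of trials, and exactly one arm in 10%, 21%, 45%, 47% and 24%. The picture is the same.

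**Reading the table.** Apart from the first row, every row is a case where both arms truly change, so a significant paired test is a correct finding of change. It is still no evidence for VR or tDCS, because in every row their effect is zero. The last column peaks where each test has about 50% power and can never exceed 50%. It should therefore be read over the whole range and not at its peak. The figures use the paired t-test. The Wilcoxon alternative has the same limit, because it also tests change from baseline.

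**The case against.** The strongest reply is that the protocol never says what a critic might fear. Its aim and hypothesis are comparative in both the Abstract and the Background. Effectiveness appears in one bullet of a value statement, beside a bullet about comparing VR with tDCS, and could be read as comparative effectiveness. The Data analysis section names separate between-group analyses. A paired test is a valid test of whether an arm changed, and two active arms without a sham are a legitimate design.

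All of that stands, and it rules out three stronger readings:

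- **That the trial's main aim is unattainable.** A reader might infer this from the effectiveness bullet. The primary hypothesis is VR against tDCS, and randomisation supports it.
- **That the arms will be compared by which one reaches significance.** A reader might infer this from the paired tests. Nothing in the document plans it. The last column of the table shows only why such a comparison would be unsafe.
- **That the paired tests are invalid in themselves.** They are valid for change. They do not attribute that change to a cause.

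The reply does not remove the gap between the bullet and the design. The bullet as worded covers both kinds of intervention and does not say relative to what. The within-arm tests carry the same threshold as the between-group analyses, with nothing to set them apart. A separate analysis plan might add such a label, but the point rests on what this document states.

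**Conclusion.** The point holds in a limited form. The design can estimate the effect of VR relative to tDCS when each is added to the same physiotherapy. It cannot show that either is effective, and the planned within-arm tests do not fill that gap. If both arms improve equally and neither add-on works, a within-arm test is significant in 5% to 93% of trials as the shared improvement goes from 0 to 8 points. Exactly one arm is significant in 10% to 48%, with the maximum of the tabulated values at 4 points. These figures rest on the assumed shared improvement, an SD of change of 8.65 and 16 analysed per arm. The conclusion about attribution needs none of them, since it follows from the two-arm design. The comparative primary hypothesis is unaffected.

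**What to change.** 1. In Data analysis, state that within-arm results are descriptive, and report the mean change in each arm with its 95% CI in place of a significance test.
2. State that all inference rests on the between-group contrast.
3. In Value of the Protocol, reword the effectiveness bullet to the relative effect of VR versus tDCS when added to the same physiotherapy.

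This changes wording only and needs no extra patients, visits or measurements. The price is a narrower claim. The Protocol validation section says that outcome data have not yet been generated, so the change can still be made before results are known.

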#### Sample size calculation

The primary outcome is fear of falling, measured by the FES‑I. As no MCID^2^ has been established for stroke patients, the MCID was estimated as 1.2 × the MDC (MDC^3^ = 6.69) based on previous studies [28,32].

Based on the standard deviation (SD) reported in the study by Molhemi et al. [9]., and according to the formula, sampsi 40.9 48.9, sd1(8.4) sd2(10.8) pre[1] post[1] r0(0.6) r1(0.6) alpha (0.05) power (0.8), assuming α = 0.05, power = 80%, and a pre–post correlation of 0.6, the calculated sample size was 16 participants per group, accounting for a 15% dropout rate [8,33].

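### The between-group comparison of FES-I is assigned to two different analyses at the same 0.05 level, and nothing says which decides the primary hypothesis

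*Protocol article*

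**What the plan says.** The Data analysis section puts the two analyses side by side: "ANOVA will be used for between‑group analyses. Between-group differences were analyzed using ANCOVA". The first is a 2 × 2 repeated-measures ANOVA. The second sentence goes on to name one covariate: "Between-group differences were analyzed using ANCOVA, with time since stroke (post-onset duration) included as a covariate". The section closes with one threshold for everything, "with significance set at p < 0.05".

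The section does not say which of the two analyses is primary, or whether the ANOVA result of interest is the group effect or the group-by-time interaction. For the ANCOVA it gives neither the dependent variable (post score or change) nor any statement that baseline FES-I is in the model.

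The Sample size calculation section identifies the endpoint ("The primary outcome is fear of falling, measured by the FES‑I") and gives the command "sampsi 40.9 48.9, sd1(8.4) sd2(10.8) pre[1] post[1] r0(0.6) r1(0.6) alpha (0.05) power (0.8", but ties it to no test. The outcome is measured twice: "A blinded assessor will evaluate outcomes at baseline and after ten physiotherapy sessions".

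**The concern.** With one baseline and one post-treatment measurement, the interaction in a 2 × 2 repeated-measures ANOVA is the same test as a t-test on change scores. An ANCOVA adjusted only for time since stroke is, if run on the post score, essentially a post-score comparison. An ANCOVA adjusted for baseline FES-I is a third test. Each holds its 5% level alone, but they use the baseline differently, differ in power and can disagree on the same data.

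With no primary analysis named, two things are at stake. If a significant result from either test may be claimed as success, the primary hypothesis is no longer tested at 5%. And when the tests disagree, the conclusion depends on which one is reported, with no pre-specified way to settle it.

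**Working it through.** **Inputs.** From the Sample size calculation section: means 40.9 and 48.9, so a difference of 8.0 (the stated rule gives 1.2 × 6.69 = 8.03); SDs 8.4 and 10.8, so a common SD of √[(8.4² + 10.8²)/2] = √93.6 = 9.67; pre–post correlation r = 0.6; α = 0.05 (sidedness not stated, taken as two-sided); power 80%; 16 per group including 15% dropout. Assumed: normal outcomes, equal baseline means by randomisation, and time since stroke uniform over 3–6 months and unrelated to outcome.

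**The plan's own figure.** n per arm = 2 × f × 93.6 × (1.96 + 0.84)² / 8², where f is the variance factor of the test. The normal-approximation power at 16 per arm is in the last column.

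| Test | f | n per arm | With 15% dropout | Power at 16 |
|---|---|---|---|---|
| Post score only | 1 | 22.96 → 23 | 28 | 65% |
| Interaction (= change score) | 2(1 − r) = 0.8 | 18.37 → 19 | 23 | 74% |
| Baseline-adjusted ANCOVA | 1 − r² = 0.64 | 14.69 → 15 | 18 | 83% |

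No row gives 16 after dropout. Baseline-adjusted ANCOVA comes closest, at 15 before dropout. A one-sided version gives 12, or 15 with dropout, but no one-sided test is stated. The sample size therefore does not reveal which test was meant. The mismatch itself is a separate matter.

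**How strongly the tests overlap.** Under the inputs above, the correlation between the interaction estimate and the other estimate is:
- post score: (1 − r)/√[2(1 − r)] = √[(1 − r)/2] = √0.2 = 0.45
- baseline-adjusted ANCOVA: √[(1 + r)/2] = √0.8 = 0.89
- change score adjusted for time since stroke: close to 1

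Lower overlap means more inflation. Two independent tests would give 1 − 0.95² = 9.75%, which is the ceiling here.

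**Simulation** (16 completers per arm, t-based tests; several runs, the described ones of 20,000 to 40,000 trials). Each row pairs the interaction with one version of the ANCOVA.

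| ANCOVA paired with the interaction | Either significant, no effect | Verdicts differ, 8-point effect |
|---|---|---|
| Change score, time since stroke | 5.7% | 4.5% |
| Post score, baseline-adjusted | 7.0–7.5% | 14% |
| Post score, time since stroke only | 9.3–9.8% | 33–34% |

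The 9.8% in one run is at the ceiling and reflects simulation error; the other runs gave 9.3%.

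Simulated power for a true 8-point effect: post score with time since stroke only, 60–61%; interaction, 71–72%; baseline-adjusted ANCOVA, 78–80%. These are a little below the normal-approximation figures, as expected with t-based inference at this size.

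**Dropout.** The 16 per group already allows for dropout: 16 × 0.85 = 13.6. With 13 completers per arm, power is about 69% for baseline-adjusted ANCOVA and 62% for the interaction.

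**The ANOVA group main effect.** This term compares the average of the pre and post scores. With equal baselines the 8-point effect becomes 8/2 = 4, with f = (1 + r)/2 = 0.8. Power at 16 per arm is 26% (normal approximation) or about 24% (simulated).

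**The case against.** The best case for the plan has three parts.

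First, the two sentences can be read as one model: the 2 × 2 repeated-measures analysis with time since stroke added as a covariate. The interaction is then a covariate-adjusted change-score test, and there is almost no multiplicity: 5.7% under the null even if both versions are run. The reading is possible, and it is why the lower end of the range is about 6%. But the text names two procedures, each for the between-group comparison, and does not say that they are one.

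Second, a condensed article may leave model details to an analysis plan that is not shown. That is fair for the ANCOVA's dependent variable or its full covariate list taken alone. It does not dispose of the point, because the article does state its between-group analysis and states two.

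Third, a reader might infer that the trial will judge treatment by the ANOVA's group main effect, and so have only about 24% power, or that counting this term as a third chance takes the error rate above 11%. The document does not support that. It never says the main effect will be read, and in a design with two groups and two visits the interaction is the natural term. What stands is narrower: the term is not named, so the wording does not exclude the wrong one.

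**Conclusion.** The concern holds as a conflict in the stated plan: two between-group analyses of the primary outcome at one 0.05 level, no rule for which decides, and the ANOVA's treatment term unnamed.

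The inflation is moderate and conditional. It arises only if either result may be claimed, which nothing in the document prevents. The risk of conflicting conclusions is larger: roughly one trial in seven to one in three with a true 8-point effect, unless the ANCOVA is on change scores, where it is 4.5%.

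These figures rest on r = 0.6, a common SD of 9.67, 16 completers per arm, and time since stroke being unrelated to outcome. Baseline-adjusted ANCOVA is preferred for efficiency; the interaction, named alone, would also be a valid 5% test. The point should be settled now, because it determines how the single primary hypothesis is decided. The Protocol validation section says recruitment is under way and no outcome data exist yet.

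**What to change.** Replace the two sentences on between-group analysis with one primary analysis: an ANCOVA of post-treatment FES-I on treatment group, adjusted for baseline FES-I and keeping time since stroke as a covariate, with the group coefficient tested at two-sided 0.05. Either delete the repeated-measures ANOVA or label it a sensitivity analysis that reports only the group-by-time interaction and cannot overturn the primary result.

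The cost is wording only. Baseline FES-I is already collected, and no visit, measurement or procedure changes. The change should be dated and recorded before any outcome data are examined by group.

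### Neither stated between-group analysis of FES-I matches the baseline-adjusted variance that the sample size needs, and neither is named as primary

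*Protocol article*

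**What the plan says.** Under Sample size calculation the protocol article states: "The primary outcome is fear of falling, measured by the FES‑I". The target difference comes from a minimal detectable change of 6.69, where "the MCID was estimated as 1.2 × the MDC". The command line compares means of 40.9 and 48.9 with SDs of 8.4 and 10.8, takes one measurement before and one after treatment, and assumes "a pre–post correlation of 0.6". Alpha is 0.05 and power 80%. The result is 16 per group, said to allow for 15% dropout. No analysis method is named there.

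Under Data analysis, between-group comparison is first assigned to a 2 × 2 repeated-measures ANOVA. The next sentence assigns it to a different model: "Between-group differences were analyzed using ANCOVA, with time since stroke (post-onset duration) included as a covariate". The reason given is possible differences in recovery status. The section does not state the dependent variable of the ANCOVA, does not mention baseline FES-I as a covariate, and does not say which of the two results decides the trial. Table 1 shows that FES-I is collected at baseline.

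**The concern.** A pre–post correlation lowers the required sample size only if the analysis uses the baseline score, and how far it does so depends on the analysis. Adjusting for baseline in an ANCOVA multiplies the variance by 1 − r². Analysing change multiplies it by 2 − 2r. Ignoring baseline leaves it unchanged. The plan's sample size and its analysis should use the same factor, and here they do not appear to.

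Time since stroke is a weak stand-in. The eligibility criteria confine it to 3–6 months, and no correlation with FES-I is given. With about 16 patients per arm there is little margin, so the choice of model decides whether the trial has roughly four chances in five or two in three of detecting its own target difference. Having two between-group tests of different precision, with neither designated, also leaves open which one answers the primary question.

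**Working it through.** **Inputs** (Sample size calculation): difference 48.9 − 40.9 = 8.0, consistent with 1.2 × 6.69 = 8.03; SDs 8.4 and 10.8; r = 0.6; alpha 0.05; power 0.80; dropout 15%. Sidedness is not stated, so two-sided is assumed.

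**Formula** (normal approximation): n per group = (1.960 + 0.842)² × (8.4² + 10.8²) × f / 8.0².

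The sum of the variances is 70.56 + 116.64 = 187.20 and the squared multiplier is 7.849, so n = 7.849 × 187.20 / 64 × f = 22.96 × f.

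**Variance factors at r = 0.6:**
- post score without baseline: f = 1
- change score, which is the group × time test of a 2 × 2 repeated-measures ANOVA: f = 2 − 2 × 0.6 = 0.80
- ANCOVA on baseline: f = 1 − 0.6² = 0.64

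**Reproducing the plan's 16.** The baseline-adjusted factor gives 22.96 × 0.64 = 14.69, so 15 per group before dropout. The standard inflation, 15 / 0.85 = 17.6, gives 18. The stated 16 appears if 14.69 is cut to 14 and multiplied by 1.15 (16.1). That route is a guess, but no other two-sided variant comes close.

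**Power** = Φ(8 / √(187.20 × f / n) − 1.960), for n = 16 evaluable per group and for n = 16 × 0.85 = 13.6:

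| Analysis | f | n before dropout | n after 15% dropout | Power, n = 16 | Power, n = 13.6 |
|---|---|---|---|---|---|
| Post score, no baseline | 1.00 | 23 | 28 | 65% | 58% |
| Change score / repeated-measures ANOVA | 0.80 | 19 | 23 | 74% | 67% |
| ANCOVA on baseline FES-I | 0.64 | 15 | 18 | 83% | 77% |

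As an example, for the change score at n = 16 the standard error is √(187.20 × 0.80 / 16) = 3.06, and 8 / 3.06 − 1.960 = 0.65, which gives 74%. With the t distribution the three figures at n = 16 are 62%, 72% and 81%.

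**ANCOVA on time since stroke alone.** Its correlation with post-treatment FES-I is not in the document. For an assumed correlation of 0 to 0.3, a post-score model needs 23 to 21 per group before dropout and has 65% to 69% power at 16. The correlation would have to be about 0.6 to bring the requirement down to 15.

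**Variance relative to baseline ANCOVA:** 0.80 / 0.64 = 1.25 for change, and 1 / 0.64 = 1.56 for the post score.

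**The case against.** The strongest reply is that the plan does use the baseline score. The repeated-measures ANOVA stands directly before the ANCOVA, and with two groups and two time points its group × time test is a comparison of change. This stands. A reader might infer that baseline imbalance goes unaddressed in the primary comparison, or that the full 1.56-fold variance penalty applies. The document supports neither: no analysis is designated primary, one of the two uses baseline, and for that one the ratio is 1.25. It still needs 19 per group before dropout, so it does not support 16.

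Second, time since stroke is named as a covariate but not as the only one, and a condensed article may leave the full covariate list elsewhere. So the text does not prove that baseline FES-I is deliberately excluded. However, the article does more than stay silent: it names a covariate and justifies it, and anyone following the section as written would fit a model that does not match the sample size.

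Third, randomisation balances baseline FES-I in expectation, and stratification by history of falls may help further. This also stands. Leaving baseline out costs precision and does not bias the comparison on average.

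Fourth, a one-sided change-score test would also give 15 per group before dropout. No one-sided test is stated.

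Finally, it is tempting to infer that adding baseline FES-I restores the planned power. After the plan's own 15% dropout it does not: 80% needs 18 per group, 36 in total against the 32 planned.

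**Conclusion.** The point holds as a mismatch between two sections of the protocol article. The sample size comes near 16 per group only with ANCOVA adjusted for baseline FES-I, while the analysis section offers a change-score comparison and an ANCOVA that names a different covariate, without choosing between them. Followed as written, the plan has about 65% to 74% power with 16 evaluable per group, and about 58% to 67% after 15% dropout, against the 80% stated. Baseline adjustment raises these to about 83% and 77%.

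These figures rest on the protocol's own difference, SDs and correlation, on a two-sided test, on the group × time term being the one read from the repeated-measures ANOVA, and, for the lower end, on an ANCOVA of the post score in which time since stroke explains little. The consequence is lost precision and an undeclared primary test.

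**What to change.** State one primary analysis: ANCOVA of post-treatment FES-I on group, adjusted for baseline FES-I, reporting the adjusted mean difference with its 95% confidence interval. Time since stroke may stay as a further covariate. Give the repeated-measures ANOVA a supporting role or drop it. For consistency, use the same form for Mini-BESTest, Biodex and 10-Meter Walk Test, each with its own baseline; the sample size argument itself concerns FES-I only.

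In Sample size calculation, name this analysis, state that the test is two-sided, and restate the power: 32 randomised gives about 77% after 15% dropout, and 80% would need 18 per group.

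The cost is a sentence or two of text, one degree of freedom and a slightly less favourable power statement. No new data are needed. Protocol validation reports that recruitment is under way and that no outcome data have yet been generated, so the change can still be made and dated before any results are seen.
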